## Abstract

**Background:**

The provision of clinically assisted hydration at the end of life is one of the most contentious issues in medicine, and indeed within the general population. The reasons for contention include: a) the lack of evidence for or against; b) the disparate opinions of healthcare professionals; and c) the generally positive opinions of patients and their carers about clinically assisted hydration.

**Methods/design:**

The study is a cluster randomised trial to assess the feasibility of conducting an adequately powered, randomised controlled trial of clinically assisted hydration in patients with cancer in the last days of life. Twelve sites, four National Health Service (NHS) hospitals and eight NHS/voluntary sector hospices in the United Kingdom, will be randomised to give either standard intervention A: continuance of oral intake and regular mouth care, or standard intervention B: continuance of oral intake, regular mouth care and clinically assisted hydration. Patients will be included if they: i) have a diagnosis of cancer; ii) are aged ≥ 18 yr; iii) have an estimated prognosis of ≤ 1 week and iv) are unable to maintain sufficient oral intake (1 L per day, measured/estimated); and v) are able to give informed consent. Patients will be excluded if they have contra-indications to receiving clinically assisted hydration. The primary endpoint of interest is the frequency of hyperactive delirium (‘terminal agitation‘), and this will be assessed using the Modified Richmond Agitation and Sedation Scale (administered every four hours). Other data to be collected include the frequency of pain, respiratory secretions (‘death rattle‘), dyspnoea, nausea and vomiting, adverse effects to clinically assisted hydration and overall survival. In addition, data will be collected on the use of anti-psychotic drugs, sedative drugs, analgesics, anti-secretory drugs and other end-of-life medication. The study has obtained full ethical approval.

**Discussion:**

A randomised controlled trial of clinically assisted hydration in end-of-life care is urgently required. This feasibility study will allow methodological and ethical issues to be understood and addressed to ensure that a robust, adequately powered, randomised controlled trial is designed.

**Trial registration:**

ClinicalTrials.gov NCT02344927 (registered 4 June 2014).

**Electronic supplementary material:**

The online version of this article (doi:10.1186/s13063-015-0988-3) contains supplementary material, which is available to authorized users.

## Background

The provision of clinically assisted hydration (CAH) at the end of life is one of the most contentious issues in medicine [1, 2], and indeed within the general population [3, 4]. The reasons for contention include: a) the lack of evidence for/against CAH [5, 6]; b) the disparate opinions of healthcare professionals about CAH [7]; and c) the generally positive opinions of patients and their carers about CAH (and the generally negative opinions about withholding/withdrawing CAH) [7]. It is, therefore, unsurprising that the provision of CAH at the end of life is extremely variable within clinical practice (12–88 % of patients with cancer in the last week of life) [8]. It should be noted that, in this instance, CAH refers to the medical provision of parenteral fluids (intravenous, subcutaneous), and not to the medical provision of enteral fluids (such as administering fluids via a gastrostomy/jejunostomy).

**Table 1 Tab1:** Standard treatment B: volume of fluid to be administered

Patient’s weight	Volume of fluid
<45 kg	1 L/24 h
45–60 kg	1.5 L/24 h
>60 kg	2 L/24 h

**Table 2 Tab2:** Overview of study assessments

Assessments	Screening	Treatment period (daily assessments)	End of study
Inclusion/exclusion criteria	X		
Consent	X		
Demographic data	X		
Cancer diagnosis	X		
Concurrent medical history	X		
Regular medication	X	X	
Oral intake	X	X	
Urinary continence	X	X	
4 hourly Modified Richmond Agitation - Sedation Scale scores		X	
4 hourly symptom occurrences		X	
As required medication		X	
Oral intake		X	
Urinary continence		X	
Parenteral fluids administered		X	
Adverse events		X	
Cannulation problems		X	
Participant outcome			X

In 2012, there were 499,331 deaths registered in England and Wales, with cancer being the most common underlying cause of death (29 % total deaths) [9]. There is limited data on the use of CAH in hospitals, and no data on the use of CAH at home or in hospices (although the impression is that CAH is generally not available in the home setting, and is generally not utilised in the hospice setting).

The lack of provision of fluids at the end of life was one of the major issues raised in the recent review of the Liverpool Care Pathway for the Dying Patient (LCP) (which has resulted in the planned withdrawal of the LCP in the United Kingdom) [10]. Indeed, the review notes that “most of the submissions to the Review from relatives and carers that were critical of the LCP made reference to hydration and nutrition”. The review comments that “if fluids are stopped without review over many days, death from dehydration will be inevitable, the lack of hydration having accelerated the dying process”. However, it also highlights that “a systematic review of all of the literature and studies evaluating the benefits of clinically assisted hydration in palliative care patients shows no clear benefit to either length or quality of life”. Of note, the aforementioned systematic review concluded that “more evidence is needed, particularly in relation to effects of clinically-assisted hydration in patients suffering symptoms that might be strongly influenced by hydration (e.g. delirium, and symptoms of fluid overload)” [6].

In 2008, Good et al. conducted a Cochrane systematic review of medically assisted hydration for adult palliative care patients, and concluded that “currently, there are insufficient good quality studies to make any recommendations for practice with regards to the use of medically assisted hydration in palliative care patients” [5]. Good et al. identified five relevant studies [11–15], although only two studies were randomised controlled studies [13, 14]. However, neither of the randomised controlled studies addressed the specific issue of the routine use of CAH at the end of life. Thus, Cerchietti et al. included patients with evidence of dehydration (and/or renal failure), and patients were given relatively low volumes of fluid (1 L per day), and the fluids were only given for 48 h (and not continued until death) [13]. Similarly, Bruera et al. only included patients with evidence of dehydration, and patients were given relatively low volumes of fluid (1 L per day), and the fluids were only continued for 48 h (and not continued until death) [14]. It should be noted that Good et al. re-searched the literature in early 2011, and although they did not find any new studies, they did identify an ongoing randomised controlled trial [16].

In 2013, Parry et al. conducted a rapid evidence review of the literature on pathways focussed on the dying phase in end-of-life care and their key components, and concluded that “the current research evidence base is not sufficient to inform specific recommendations to use or not to use clinically-assisted nutrition and/or hydration” [6]. The review included the new randomised controlled trial [16], which again did not address the specific issue of the routine use of CAH at the end of life. Thus, Bruera et al. only included patients with evidence of dehydration, and patients were given relatively low doses of fluid (1 L per day), and the fluids were continued for a variable duration, that is, “until the patient was unresponsive, developed progressive coma, or died”. The conclusion of this study was that “hydration at 1 L per day did not improve symptoms, quality of life, or survival”.

The purported positive effects of CAH include the maintenance of patient comfort (for example, prevention of thirst, prevention of dry mouth), and the maintenance of renal perfusion/prevention of accumulation of toxins and drugs (prevention of delirium, prevention of opioid toxicity) [17]. In contrast, the purported negative effects of CAH include problems due to fluid overload (for example, worsening of peripheral oedema, worsening of cardiac failure), and problems due to fluid-related complications (for example, worsening of vomiting, worsening of respiratory secretions) [17]. In addition, it has been claimed that ketones and other by-products of dehydration can have positive effects on the patients’ condition/symptom control (analgesic effects, sedative effects). As intimated above, there is little evidence to support/refute these effects in the general population.

Patients with cancer may develop a range of problems in the last days of life, including delirium (’terminal agitation’/’terminal restlessness’ [18]), excess respiratory secretions (’death rattle’), urinary retention or urinary incontinence, and continuance or exacerbation of other symptoms (for example, pain, dyspnoea, nausea and vomiting) [19].

Delirium is one of the most common problems (25–85 % of patients) [20], and one of the most distressing problems (for patients, relatives and healthcare professionals) [21], encountered at the end of life. Dehydration is a recognised cause of delirium, and rehydration a recommended intervention for delirium (in appropriate situations) [20]. Nevertheless, the mainstay of the management of delirium is the use of antipsychotic and/or sedative drugs [20]. Such agents are used in approximately 50 % of patients in the last week of life [22], and although they are generally very effective, they are often associated with untoward sedation (which necessarily impacts the dying process, especially in terms of interpersonal communication). It should be noted that the use of sedative drugs was another major issue raised in the recent review of the LCP (which has resulted in the planned withdrawal of the LCP in the United Kingdom) [10].

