### Inclusion/exclusion criteria for participants and recruitment

Up to 200 patients will be included in the trial. Patients are eligible for inclusion if they have a diagnosis of cancer; are aged 18 years or above; have an estimated prognosis of ≤ 1 week; and are unable to maintain sufficient oral intake (1 L per day, measured/estimated). Patients will be excluded if they are clinically dehydrated; have a relevant advance directive to refuse treatment; have a clinical indication for clinically assisted hydration (for example, hypercalcaemia); have a clinical contra-indication to clinically assisted hydration (for example, cardiac failure); have a clinical contra-indication to peripheral cannulation; are already being administered intravenous fluids/subcutaneous fluids/total parenteral nutrition (TPN)/enteral feeding or fluids; have symptoms of delirium at the time of consent or have experienced symptoms of delirium in the previous 24 hours; or are likely to be transferred to another setting for endof-life care (for example, home, hospice).

Potential participants will be highlighted to the research team by the clinical team; the research team will then screen the patient for eligibility to enter the study. If the patient is deemed to have capacity by the clinical team, then consent will be sought from the patient in the normal manner by the research team Additional file 1.

If the patient is deemed not to have capacity, then a personal consultee (that is, “someone who has a role in caring for the person who lacks capacity or is interested in that person’s welfare but is not doing so for remuneration or acting in a professional capacity”) will be approached for advice re the patient entering the study [24, 25]. In this study, the personal consultee could be a relation of the person or a friend of the person. The personal consultee will be given an information sheet about the study, given the opportunity to ask questions about the study, and asked whether in their opinion the patient would have any objection to taking part in the study.

If the patient is deemed not to have capacity, and no personal consultee is available, then a nominated consultee will be approached for advice re the patient entering the study [24, 25]. In this study, the nominated consultee will be the Study Guardian (who is independent of the research team).

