### Study procedures

During the treatment period patients will be reviewed at least every four hours, and an assessment made as to whether or not certain symptoms are present, that is, hyperactive delirium (‘terminal agitation‘), pain, excess respiratory secretions (‘death rattle‘), nausea and vomiting, dyspnoea and urinary continence. Agitation will be given a score (see below), but the other symptoms will simply be recorded as present or absent. In addition, changes in regular medications, use of as required (PRN) medications, oral intake, urinary continence, and (if appropriate) parenteral fluids administered, adverse events relating to parenteral fluids and requirements for re-cannulation will also be noted. Data will be obtained from the participant’s observation chart and the participant’s drug chart(s); these documents are considered source documents in this study.

At the end of the study the researcher will record the participant’s outcome, including the date of death/withdrawal, and the reason for withdrawal (if appropriate). The end of study occurs when an individual participant either: a) survives for ≥ 14 days; b) dies (expected outcome); or c) is withdrawn from the study Table 2.

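### Pain, respiratory secretions, dyspnoea and nausea/vomiting have no scheduled entry record, so their secondary frequencies can mix symptoms present at entry with those arising under allocated care

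*Protocol article*

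**What the plan says.** The Abstract (Methods/design) lists the symptom outcomes: "Other data to be collected include the frequency of pain, respiratory secretions", followed by dyspnoea and by nausea and vomiting. The Trial design section says that primary and secondary endpoint data will be used to design the later RCT.

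Table 2, printed in the Background section, has a row "4 hourly symptom occurrences" marked for the treatment period, with the Screening cell blank. Regular medication, oral intake and urinary continence are marked at both Screening and treatment. Study procedures places the symptom review in the treatment period, at least every four hours, and fixes the scale: "Agitation will be given a score (see below), but the other symptoms will simply be recorded as present or absent".

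The only symptom-based entry exclusion concerns delirium. Patients are excluded if they "have symptoms of delirium at the time of consent or have experienced symptoms of delirium in the previous 24 hours". The four other symptoms are not in the list.

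The Background says that patients in the last days may have "continuance or exacerbation of other symptoms (for example, pain, dyspnoea, nausea and vomiting". It also lists, among the purported negative effects of fluid, "worsening of vomiting, worsening of respiratory secretions".

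**The concern.** Delirium is in effect an incident outcome, because current and recent cases are kept out. The other four symptoms get neither an exclusion nor a scheduled entry value. A patient who arrives in pain or short of breath can then be charted with that symptom from the first observation, whatever care the site was allocated.

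Two things are at stake. First, symptoms already present in both arms dilute a real difference in new symptoms. Second, sites rather than patients are randomised, and there are only 12, so the arms may differ at entry; without a pre-treatment value that difference has no direct check and no direct adjustment. Sites also know their allocation when the clinical team puts patients forward, and an entry record is the direct way to see whether that changed who was referred.

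The schedule of data collection fixes this point. A later analysis plan can choose how to summarise the charts, but it cannot recover a pre-treatment value that was not collected.

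**Working it through.** The article gives no rate, margin or sample size for these symptoms, so there is no stated figure to reproduce. The check reads the schedule against the text and then illustrates size on labelled assumptions.

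**Reading the schedule**

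| Item | Screening record | Treatment record | Entry exclusion |
|---|---|---|---|
| Regular medication, oral intake, urinary continence | Yes | Yes | Oral intake is an inclusion criterion; the others have none |
| Delirium/agitation | Assessed for eligibility | 4-hourly mRASS | Yes |
| Pain, secretions, dyspnoea, nausea/vomiting | None scheduled | 4-hourly, present/absent | None |

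**Inputs from the article:** 12 sites and 200 participants, hence 200/12 = 16.7 per site, taken below as 6 sites of 17 per arm (102 patients).

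**Assumed inputs:** the endpoint is symptom ever recorded; entry prevalence *b*; new-onset risk *h* among those free at entry; between-site coefficient of variation (CV) of entry prevalence *k*, either 0 or 0.25.

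**Dilution.** Ever recorded = *b* + (1 − *b*)*h*. With the same *b* in both arms, the difference is (1 − *b*)(*h*_B − *h*_A).

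- *b* = 0.40, *h* = 0.30: 0.40 + 0.60 × 0.30 = 0.58
- *b* = 0.40, *h* = 0.45: 0.40 + 0.60 × 0.45 = 0.67
- Difference 0.09, against a true new-onset difference of 0.15

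For the same 15 points, the recorded difference is 13.5 at *b* = 0.10, 12.0 at 0.20, 10.5 at 0.30 and 7.5 at 0.50.

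**Apparent effect from entry imbalance alone.** With *h* = 0.30 in both arms:

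- *b* = 0.30: 0.30 + 0.70 × 0.30 = 0.51
- *b* = 0.40: 0.40 + 0.60 × 0.30 = 0.58

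A 10-point entry imbalance gives a 7-point difference with no effect of hydration.

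**How often chance gives such an imbalance.** For prevalence *p*, the variance of the between-arm difference is 2 × [(*kp*)² + (*p*(1 − *p*) − (*kp*)²)/17] / 6. A difference of at least 10 points means at least 11 patients of 102 (10/102 = 0.098 falls short), so with continuity correction the cut is 10.5/102 = 0.103.

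| *p* | *k* | Variance | SD | z | Chance of ≥ 10 points |
|---|---|---|---|---|---|
| 0.30 | 0 | 0.00412 | 0.064 | 1.60 | 11% |
| 0.40 | 0 | 0.00471 | 0.069 | 1.50 | 13% |
| 0.30 | 0.25 | 0.00588 | 0.077 | 1.34 | 18% |
| 0.40 | 0.25 | 0.00784 | 0.089 | 1.16 | 25% (24.5) |

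Beta-binomial simulation agrees with each row to within rounding. The calculation ignores the separate randomisation of hospitals and hospices, which would reduce imbalance to the extent that symptoms differ by setting.

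**The case against.** The strongest reply is that this is a condensed article with an overview table. The table is loosely drawn: oral intake and urinary continence each appear twice with different marks, and the mRASS row is blank at screening although delirium must be assessed for eligibility. Concurrent medical history and regular medication are recorded at screening, and the CRF is not shown. That is fair, but Study procedures says the same as the table, and the article gives neither screening item the role of a symptom baseline.

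A second reply is that the endpoint derivation is not stated. The analysis plan might use the proportion of observations, change over time, or the first 4-hourly chart as a near-baseline. This stands as a limit on size: the dilution figures hold only for an ever-recorded endpoint. The first chart, however, falls after allocated care has started.

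Third, chance imbalance adds variance and does not bias a randomised comparison, and total symptom burden is a legitimate quantity at the end of life. Both are right. More than half of the imbalance probability at a CV of 0.25 is already there with no between-site variation (11 of 18, 13 of 25). An entry value would still improve precision and let case mix be checked.

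A reader might go further and infer that the plan fails to show the worsening it names as a harm. The documents do not support that. The Abstract undertakes to collect frequency only. Worsening is Background text on purported effects and, among these four symptoms, names only vomiting and secretions. Secretions are also not among the symptoms that the Background describes as continuing. And since "the other symptoms will simply be recorded as present or absent", a single entry value would not show worsening of a symptom already present. Nor can one say that entry differences are wholly beyond checking, because the first chart gives an imperfect proxy.

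**Conclusion.** The point holds in a limited form. As scheduled, the secondary frequencies of these four symptoms can mix pre-existing with new symptoms, and no pre-treatment value is planned with which to check or adjust for entry differences across 12 randomised sites. The direction of the dilution follows for any non-zero entry prevalence if the endpoint is ever recorded. The sizes (15 points reduced to 9; imbalance of 10 points or more in 11–13% or 18–25% of trials) rest on assumed prevalences, onset risks and CV, none of them from the article.

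No stated figure changes. The primary outcome is unaffected, since patients with current or recent delirium are excluded, and the planned sample size for the definitive study uses delirium only. This is a worthwhile, inexpensive improvement to secondary data in a feasibility trial whose charts a definitive trial could inherit.

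**What to change.** Mark the symptom row under Screening in Table 2. Record pain, excess respiratory secretions, dyspnoea, and nausea and vomiting once each as present or absent, before that participant's allocated care starts. Report each secondary symptom in all participants adjusted for its entry value, with new occurrence among those free of it at entry as a supporting analysis. This separates new from pre-existing symptoms; it should not be presented as a measure of worsening.

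The cost is one extra line on an existing chart and a small CRF change. Recruitment began on 20 February 2015, so patients enrolled before the change will have the entry value missing or taken from the notes; the report should say which and how many.

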### Study rationale and aim

The authors of the Cochrane systematic review discussed the need for further studies in this area, and highlighted the barriers to conducting such studies, including obtaining informed consent, recruitment of subjects, retention of subjects, and presence of confounders [5, 23]. Our aim is to undertake a cluster randomised trial of clinically assisted hydration in non-dehydrated cancer patients at the end of life (that is, in the last week of life) in order to fully assess the practical and ethical issues that need to be addressed in a randomised controlled trial (RCT) and to provide data to adequately power the RCT.

## Methods

### Trial design and setting

The study will be a multi-centre cluster randomised trial carried out in NHS hospitals and NHS/voluntary sector hospices in the United Kingdom. Twelve sites (four hospitals, eight hospices) will participate in the feasibility study and will be randomised to either standard treatment A or standard treatment B. The Surrey Clinical Trials Unit, Surrey CRC, University of Surrey will be responsible for the cluster randomisation, trial management, data management and analysis.

The trial will assess the feasibility of a multi-centre RCT by identifying and addressing the methodological and ethical issues raised. It will provide primary and secondary endpoint data in order to design an appropriately powered RCT.

The trial has been funded by the Research for Patient Benefit Programme of the National Institute of Health Research (National Health Service) and has received a favourable ethical opinion from the London-Bromley National Research Ethics Service (NRES) Committee (reference 14/LO/1543), and the University of Surrey Research Ethics Committee. The trial, current protocol, version 5, 23 February 2015, is registered on ClinicalTrials.gov NCT02344927 (registered 4 June 2014).

Full informed written consent will be obtained from all patients, or their designated consultee, prior to enrolment in the trial.

